#### Sample size estimation

The sample size was estimated by simulation [61, 62]. The sample size simulation was performed in four steps: (1) defining the sample size problem and outcomes; (2) defining, writing and running the sample size simulation algorithm; (3) estimating the possible outcomes derived from the simulations; (4) finding the optimal sample size.

In step 1, the sample size problem was developed considering the following objective: to estimate the minimum sample size required to comply with a maximal type I error (*α*) of 0.05 or 5% and a maximal type II error (*β*) of 0.20 or 20%. The input outcomes were: populational mean pain intensity (0–10) of 6.0 with a standard deviation (SD) of 2.3; a hypothesised minimal clinically important difference (MCID) in pain intensity between groups of -1.0 with an SD of 0.25 [63]; three groups; three repeated measurements (baseline, 10 weeks and 6 months); a correlation within the repeated measurements of 0.30 or 30% [64]; a minimum of 30 participants per cluster (five physiotherapy facilities); a correlation within clusters of 0.20 or 20% [65]; and a loss to follow-up of 30% [66].

In step 2, the simulation algorithm was defined and written in R language [67]. The input outcomes defined in step 1 were then included in the algorithm. Normal distributions were simulated using the input means and SDs set in step 1 as hyperparameters. The simulations were gathered running the distributions considering several possible sample sizes for one group ranging from 5 to 5000 in 32 steps (i.e., 5 to 50 by 5; 60 to 100 by 10; 150 to 500 by 50; 600 to 1000 by 100; and 2000 to 5000 by 1000), with 100 replications for each step, and repeating this procedure 10 times (i.e., 10 iterations), summing up 32,000 sample size simulations in total.

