In step 3, we estimated summary statistics for the simulated distributions in each of the 32 possible sample sizes, including the probability of type I error (*α*), type II error (*β*) and power (1-*β*). In step 4 we found the minimum sample size required to achieve the pre-defined type I error (*α* ≤ 0.05 or 5%), type II error (*β* ≤ 0.20 or 20%) and power (≥ 0.80 or 80%). At this moment the suggested minimum sample size was 80 participants per group. Then, corrections for loss to follow-up and correlations amongst the five clusters (physiotherapy facilities) and repeated measurements were applied [64, 65]. The sample size simulation suggested a minimum sample size of 105 participants per group, that is, 315 participants (105 in each treatment group) in total for this study.

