#### Quantitative data analysis

For continuous variables, we will calculate statistics of central tendency and dispersion, such as means and, standard deviation. For categorical variables, we will describe frequencies and absolute numbers. Normality will be investigated by visual inspection of histograms. The baseline characteristics of the participants and implementation outcomes will be calculated using descriptive statistics. The differences between groups and the 95% confidence interval will be calculated using mixed models. The fixed effect term will be composed of dummy variables indicating groups, and follow-up time-points, that is, 10 weeks and 6 months after baseline, and the interaction terms composed of group and time. The estimates will be adjusted for any potential differences that might exist at the baseline. The random effect term will be composed of: (1) a correlated random intercept and slope varying the intercept for the five physiotherapy clusters and varying the slope for time points; and (2) a correlated random intercept and slope varying the intercept for repeated measurements within each cluster and varying the slope for time-points [69].

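### Primary effectiveness (pain) model: under dummy-coded time the random part has one redundant variance parameter, and the baseline adjustment is left open although literacy is tied to arm by design

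*Protocol article*

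**What the plan says.** Under Quantitative data analysis, between-group differences with 95% confidence intervals come from mixed models. The fixed part has dummies for group and for "follow-up time-points, that is, 10 weeks and 6 months after baseline", plus their interaction.

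The random part has two terms. The first is "a correlated random intercept and slope varying the intercept for the five physiotherapy clusters and varying the slope for time points". The second is "a correlated random intercept and slope varying the intercept for repeated measurements within each cluster and varying the slope for time-points". The text does not say whether baseline is an outcome row, or whether the slope refers to the dummies or to time as a number. Sample size estimation counts three repeated measurements, baseline included.

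On covariates there is one sentence: "The estimates will be adjusted for any potential differences that might exist at the baseline". No variable is named.

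Under Procedures and randomisation, people who cannot read or write Portuguese are randomised in a separate first step, to the synchronous or video arm only. Everyone else is randomised to all three arms. Randomisation is stratified by the five physiotherapy centres.

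**The concern.** There are two separate faults in stated rules.

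First, a random intercept and a random slope on time dummies already saturate a participant's covariance matrix. A residual variance on top is one parameter too many. An analyst whose software rejects the model has to simplify it, and the text does not say how. The precision of the main comparison would then depend on a choice made with the data in hand. The centre term asks five units to support an intercept variance, a slope variance and their covariance.

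Second, the natural reading of the covariate sentence is that observed baseline imbalance decides what is adjusted for, so the adjusted estimate is not fixed beforehand. Two variables that belong in the model whatever the data show are not secured. One is baseline pain, which predicts follow-up pain. The other is the literacy step, whose distribution differs between arms because of the design and not by chance.

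**Working it through.** The plan gives no figure of its own to reproduce here. The inputs come from Sample size estimation: pain "of 6.0 with a standard deviation (SD) of 2.3"; "minimal clinically important difference (MCID) in pain intensity between groups of -1.0 with an SD of 0.25"; within-person correlation 0.30; within-centre correlation 0.20; five centres; 30% loss; 105 per group. The type I error is 0.05, taken as two-sided because sidedness is not stated. Term (2) is read as participant within centre.

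**1. Two follow-ups as outcomes.** Let a be the intercept variance, b the slope variance, c their covariance and s the residual variance. A participant's covariance matrix is

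- V11 = a + s
- V12 = a + c
- V22 = a + 2c + b + s

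That is 4 unknowns for 3 elements (rank 3). Raising s by δ, lowering a by δ, raising c by δ and lowering b by 2δ leaves all three elements unchanged. With variance 2.3² = 5.29 and covariance 0.30 × 5.29 = 1.587, both of these sets fit exactly:

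- s = 1, a = 4.29, c = −2.703, b = 5.406
- s = 2, a = 3.29, c = −1.703, b = 3.406

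**2. Other readings of time.**

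| Reading | Participant level: parameters / elements / rank | With centre term: parameters / rank |
|---|---|---|
| Two follow-ups, dummy | 4 / 3 / 3 | 7 / 6 |
| Three occasions, two dummies | 7 / 6 / 6 | 13 / 12 |
| Three occasions, linear slope | 4 / 6 / 4 | 7 / 7 |

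Only the linear-slope reading is identified.

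**3. Effect on the contrast.** Data were simulated with five centres, 315 participants and the inputs above, under the two-follow-up reading. The correlation of centre effects between visits was assumed to be 0.8. The residual variance was then fixed in turn at 0.5, 1.0, 1.5, 2.0 and 2.5. Every fit gave −2 REML 1526.1803, a 6-month difference of −1.1945 and an SE of 0.2791. The group contrast does not depend on the undetermined split.

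**4. Software behaviour.** No software is named for this model. The R package lme4 is used here as an assumption, on a second simulated data set. It stops by default under both dummy readings: 630 observations against 630 participant random effects, and 945 against 945. With that check switched off, both fit. With two follow-ups as outcomes:

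| Model | 10-week difference (SE) | Interaction (SE) |
|---|---|---|
| Full, check off | −0.83 (0.260) | −0.335 (0.339) |
| Random intercepts only | −0.83 (0.278) | −0.335 (0.339) |

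The 10-week SEs differ by 0.278/0.260 = 1.07.

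**5. Five centres.** Under the assumptions of step 3, the centre intercept-slope covariance was singular in 23 of 200 simulated trials (11.5%).

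**6. Baseline pain.** Evaluable per arm: 105 × 0.70 = 73.5, so 145 degrees of freedom. For one pairwise comparison at one visit, ignoring clustering:

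- No adjustment: SE = 2.3 × √(2/73.5) = 0.379; 1.0/0.379 = 2.64; power 74.5% (noncentral t).
- Adjustment at r = 0.30: residual variance × (1 − 0.30²) = 0.91; SD = 2.3 × √0.91 = 2.194; SE = 0.362; 1.0/0.362 = 2.76; power 78.4%.

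**7. Literacy.** Let q be the share of randomised participants who cannot read or write. If they split equally over two arms and the others equally over three, the share in the synchronous and video arms is (q/2)/(q/2 + (1 − q)/3) = 3q/(2 + q). In the e-book arm it is 0. The documents do not give q or the outcome difference by literacy, so no size is put on the resulting bias.

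**The case against.** - *The answer does not change.* With dummy coding, the redundant structure reproduces an unstructured within-person covariance, which is what a repair would specify. Step 3 confirms that the contrast and its SE are unaffected. This stands, so the redundancy is a fault of specification and does not bias the result.
- *An identified reading exists.* If baseline is an outcome and the slope is linear in time, the model is identified. This also stands. The dummies and the slope on time-points favour the other readings, but the text does not settle it.
- *The covariate sentence states no test or selection rule.* It may mean the baseline value of the outcome, or that the interactions are net of the baseline difference. Either is possible. Neither is said, and neither would bring in literacy.
- *Covariate lists and fallbacks usually sit in an analysis plan, which is not shown.* That is fair for an omission. Here the article states an adjustment rule and a random structure, and both are loose as written.
- *A reader might infer that the model cannot be run.* The documents do not support that. No software is named, and the model fits in lme4 once one default check is switched off.
- *A reader might infer that SEs are too small by √1.30 = 1.14 because within-person correlation is ignored.* That needs term (2) to be a second centre-level term duplicating the first, and an effect averaged over visits. The plan targets group-by-time differences.

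**Conclusion.** The point holds in a limited form, and for the primary effectiveness outcome only; implementation outcomes are analysed descriptively.

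Under either dummy reading the random part has exactly one redundant parameter, and the centre-level slope rests on five units. Estimates of group differences survive. What is exposed is the choice of a reduced model after a software refusal, which moved one SE by about 7% in a single simulated data set and left the coefficients unchanged. That figure is an illustration and not an expected value.

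The adjustment sentence matters more in practice. It does not fix the covariates, and literacy is associated with arm by design in any contrast involving the e-book arm. The power gain of about 4 points compares always adjusting for baseline pain with never adjusting. It assumes that the plan's correlation of 0.30 holds between baseline and follow-up, and it overstates the gain if the plan's own adjustment would have included baseline pain.

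**What to change.** Rewrite the model paragraph as follows:

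- Outcome rows: pain at 10 weeks and at 6 months.
- Pre-specified fixed terms: arm, visit, arm by visit, baseline pain and literacy randomisation step.
- Physiotherapy centre, the stratification factor, as a simple effect (fixed, or a random intercept) without a slope.
- One identified within-person covariance, for example an unstructured 2×2 matrix per participant, with no further participant-level random terms.
- Delete the sentence on adjusting for whatever differences exist at baseline.

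Kenward-Roger degrees of freedom and the choice of fixed over random centre effects are optional.

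The cost is one paragraph and a few degrees of freedom (four if centre is fixed). No new data are needed: baseline pain, centre and the randomisation step are already recorded or known. The change should be dated before any outcome data are compared by arm.

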#### Economic evaluation

The economic evaluation will be conducted with an ITT approach. The cost-effectiveness analysis will be conducted using pain (measured by the numerical pain scale after 6 months of randomization). The cost-utility analysis will be conducted using quality-adjusted life-years (QALYs). The QALYs will be estimated from the evaluation of the health status of the participants using the EQ-5D-3L instrument. These health states of the descriptive system of the EQ-5D-3L will be converted into utility values using Brazilian tariffs [54]. Finally, the QALYs will be calculated from the linear interpolation between measurement points using the utility values of the participants collected at baseline, 10 weeks, and 6 months after randomization.

The average cost differences between groups will be calculated for SUS and societal perspectives and disaggregated by cost categories. The average cost and effect differences will be estimated by unrelated regression analyses. The incremental cost-effectiveness ratios will be calculated by the difference between the costs of the interventions divided by the difference between the effects of these interventions. Bias-corrected and accelerated bootstrapping techniques (5000 replications) will be performed to estimate the uncertainty surrounding cost difference and incremental cost-effectiveness ratios. The cost-effectiveness pairs from the 5000 replications will be presented graphically in a cost-effectiveness plane. Cost-effectiveness acceptability curves will be estimated to indicate the probability of interventions being cost-effective compared to each other at different willingness-to-pay thresholds [70].

Multiple imputations by chained equations will be used to handle the missing cost and effect data. An imputation model will be developed and will include sociodemographic and anthropometric variables, duration of symptoms and all available values of costs and effects measured at baseline and follow-up periods. Ten complete datasets will be created (considering loss of efficiency < 5%). The grouped estimates will be calculated according to Rubin’s rules [71].

To evaluate the robustness of the results, two exploratory sensitivity analyses will be performed. The first sensitivity analysis will be performed by excluding the total costs of the e-book and the asynchronous video development and editing. The second sensitivity analysis will be performed considering only patients with more than 75% of adoption of the intervention. The economic evaluation will be conducted at RStudio.

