### Procedures and randomisation

Individuals referred to the EducaDor programme will first be contacted by a researcher ([name]; [name]) via an electronic videoconferencing system at the scheduled consultation. During this initial contact, the researcher will screen the participant for eligibility and provide information about the EducaDor programme, as well as the name of the referred physiotherapy centre. Eligible participants will receive a link to an online consent form via email or text message, which they can accept to participate. Once the consent form is accepted, one researcher will conduct the baseline assessment, and another researcher will randomly assign the participant to one of the intervention groups.

Participants included in the study will receive physiotherapy-based care and the *EducaDor* programme as per randomisation into three different modes of delivery: (1) synchronous online group; (2) asynchronous videos group; or (3) interactive e-book group. Although the three groups have the interactive e-book, the synchronous online group and the asynchronous videos group receive additional types of digital content that are accessible to participants who cannot read and/or write in Portuguese. Then, the first step of randomisation will be done for participants who cannot read and/or write in Portuguese into (1) synchronous online group or (2) asynchronous videos group. The second step of randomisation will include all other eligible participants into the three different modes of delivery: (1) synchronous online group; (2) asynchronous videos group; or (3) interactive e-book group.

One researcher ([name]) will perform a stratified block randomization within the five physiotherapy centres accredited at SUS in the city, at the ratio of 1:1, using Excel software. The randomised list will be under the custody and confidentiality of the researcher ([name]). One week before the start of the *EducaDor* programme, one researcher ([name]) will send a list of participants to the researchers responsible for the interventions ([name], [name], [name], and [name]). The intervention researchers will then contact the participants to explain the intervention according to group allocation.

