**Fig. 3 Fig3:**
[figure not shown]
Adaptation of Proctor’s conceptual model of implementation research

The primary implementation outcomes will be cost-effectiveness, adoption, and acceptability (satisfaction using a numerical scale from 0 to 100). Primary and secondary implementation outcomes are described below and summarized in Table 1.*Acceptability* will be analysed from the perspective of the organisation through a focus group, from the perspective of end-users through an individual qualitative interview about satisfaction with the intervention, and by a numerical scale from 0 to 100 on how satisfied they were in participating in the intervention. The acceptability of the implementation will also be evaluated by the Acceptability of Intervention Measure (AIM) [47] in organisations and end-users. The AIM has four questions with a Likert scale from 1 (completely disagree) to 5 (completely agree), and the mean of the score will be used (1 to 5). Higher scores indicate greater acceptability [47].*Appropriateness* will be analysed from the end-users’ perspective regarding the perception of the appropriateness of each component of the *EducaDor* programme about their health condition through an adapted questionnaire [48]. This questionnaire will assess the degree to which participants agree with a series of statements about the intervention, on a Likert scale from 1 (totally disagree) to 4 (totally agree). The appropriateness of the implementation will also be evaluated by the Intervention Appropriateness Measure (IAM) [47] in the organisation and end-users. The IAM score is the same as the AIM.*Feasibility* will be evaluated from the perspective of the organisation and individual providers through a focus group, and the Feasibility of Intervention Measure (FIM) [47] will be used in participants, organisations and individual providers. The FIM score is the same as the AIM and AIM.*Adoption* will be analysed by the percentage of acceptance of public health users to participate in the *EducaDor* programme referred from primary healthcare. We will contact by telephone those public health users who refuse to participate by inviting them to an individual qualitative interview to identify barriers to engagement in the *EducaDor* programme.*Fidelity* will be evaluated by an independent pain specialist ([name]), who will randomly select 10% of the recorded meetings and evaluate the intervention providers in relation to the fidelity of the intervention manuals with the content and quality of the meetings in a qualitative individual interview.The adherence of participants with the *EducaDor* programme will be measured by the frequency rate in synchronous meetings; self-rated performance of proposed homework on a numerical scale from 0 to 10 during the intervention period; and by exercise adherence scale (EARS-Br) [49].*Penetration* will be analysed descriptively from the rate of public health users referred from each primary healthcare unit.*Sustainability* will be evaluated by a focus group with public health managers after the presentation of the results of the study to discuss the maintenance of the *EducaDor* programme, and by a response rate of synchronous group users and reasons for discontinuity of the programme through an individual qualitative interview.*Costs* will be estimated from the SUS and societal perspectives in a time horizon of 6 months. The SUS costs will include the intervention costs and healthcare utilization costs covered by SUS. The intervention costs will be determined by preparation, video recording, development and editing, maintenance and support technology costs, monitoring data costs and staff, training health professionals and project management costs, number and duration of phone calls and the number of text messages sent to participants. The e-book and asynchronous intervention costs will be diluted in 10 years. The healthcare utilization costs covered by SUS will include prescribed drugs, medical consultations, physiotherapy-based care, visits to specialists, diagnostic exams, emergency services and hospitalisation. The societal costs will include the SUS costs, private healthcare costs, patient costs (out-of-pocket expenses with unprescribed drugs, complementary costs, and transportation costs), and lost productivity costs (related to absenteeism). The quantities of resource utilization will be identified by the participants in a self-rated diary cost that will be provided at baseline and an assessor will collect this information by telephone every 3 months. The healthcare utilization costs covered by SUS will be valued using the Brazilian standard costs [50]. Patient costs will be valued using the out-of-pocket expenses reported by patients. Private transportation will be valued by the price of Brazilian gasoline per kilometre and public transportation by the reference price of Guarapuava city. The lost productivity costs will be estimated from the hours of absenteeism to work (paid and unpaid) through a questionnaire, and evaluated according to the Human Capital Approach and will be valued using gender-specific price weights [50].

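### The economic analysis as described has no term for physiotherapy centre, the randomisation stratum, so its intervals tend to be conservative by an amount that depends on the ICC

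*Protocol article*

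**What the plan says.** All references are to the protocol article.

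- **Status of the outcome** (Implementation outcomes): "The primary implementation outcomes will be cost-effectiveness, adoption, and acceptability".
- **Randomisation** (Procedures and randomisation): one researcher "will perform a stratified block randomization within the five physiotherapy centres accredited at SUS in the city". Individuals are allocated, and centre is the stratum.
- **Sizing** (Sample size estimation): the inputs for pain include "a correlation within clusters of 0.20 or 20" per cent, an SD of 2.3, a difference of 1.0 and 30% loss to follow-up.
- **Clinical model** (Quantitative data analysis): a mixed model with a random effect "varying the intercept for the five physiotherapy clusters".
- **Economic model** (Economic evaluation): "The average cost and effect differences will be estimated by unrelated regression analyses". The effect measures are 6-month pain and QALYs. Uncertainty comes from a bias-corrected and accelerated bootstrap with 5000 replications. No covariates and no resampling scheme are given.
- **Imputation** (Economic evaluation): "An imputation model will be developed and will include sociodemographic and anthropometric variables, duration of symptoms", together with the available cost and effect values. Centre is not listed.

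**The concern.** The article treats centre as important in three places and then describes the economic analysis, which supplies a primary implementation outcome, without it. When arms are balanced within centre, differences between centres cancel from the arm contrast. A regression on arm alone still counts those differences as residual noise, so the reported standard error exceeds the true sampling variability. A bootstrap that resamples without regard to centre has the same property.

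At stake is precision: wider intervals for cost and effect differences, and more spread in the cost-effectiveness plane, than the design requires. Costs could plausibly vary by centre, because each participant's physiotherapy is delivered at one. If imputation also omits centre, imputed values are drawn towards the overall mean and weaken the centre differences, and the plan allows for 30% loss to follow-up.

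**Working it through.** **1. The plan's own figures.** The article gives no sample size or power for the economic evaluation. For pain it gives 80 per group before corrections. The usual two-sided formula gives 2 × (1.96 + 0.842)² × 2.3² / 1.0² = 83.0, so 84; power at 80 per group is 0.785. The step from 80 to 105 cannot be traced to one correction: dividing by 0.7 gives 115, multiplying by 1.3 gives 104, and other combinations land at 103 to 105. None of this bears on the present point. The inputs carried forward are SD 2.3, ICC 0.20 and five centres.

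**2. Inflation by formula.** I read the named method as seemingly unrelated regression; with the same regressors in both equations it equals ordinary least squares for each. Let σ² be the total variance and arms be balanced within centre.

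- True variance of the arm contrast is proportional to σ²(1 - ICC).
- Without centre, the model estimates it from about σ². Ratio of standard errors: 1/sqrt(1 - ICC).
- With only five centres, the observed between-centre variance averages 4/5 of its population value, so the estimate is nearer σ²(1 - ICC) + 0.8 × σ² × ICC. Ratio: sqrt((1 - 0.2 × ICC)/(1 - ICC)).

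| ICC | 1/sqrt(1 - ICC) | Five-centre version | Simulated ratio of mean CI widths |
|---|---|---|---|
| 0.20 | 1/sqrt(0.80) = 1.118 | sqrt(0.96/0.80) = 1.095 | 1.455/1.329 = 1.095 |
| 0.05 | 1/sqrt(0.95) = 1.026 | sqrt(0.99/0.95) = 1.021 | 1.474/1.444 = 1.021 |
| 0.01 | 1/sqrt(0.99) = 1.005 | sqrt(0.998/0.99) = 1.004 | not run |
| 0 | 1.000 | 1.000 | 1.485/1.486 = 1.00 |

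The two formulas give the ranges of 9 to 12% at 0.20 and 2 to 3% at 0.05. The ratio does not depend on the number per arm.

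**3. Simulation.** Two arms, five equal centres, 15 per arm per centre (75 per arm, close to 105 × 0.7 = 73.5), total SD 2.3, 3,000 runs. At ICC 0.20 with no true difference:

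- centre omitted: coverage 0.969, type I error 0.031;
- centre included: coverage 0.953, type I error 0.047.

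The direction is therefore conservative. A separate run at 73 per arm gave mean widths of 1.47 and 1.34 points.

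**4. Bootstrap.** A percentile bootstrap (not the planned bias-corrected version) at ICC 0.20 gave mean widths of 1.429 resampling within arm only and 1.265 resampling within centre and arm. The ratio of 1.13 slightly overstates the gain. Resampling cells of 15 shrinks the variance by 14/15, about 3% in width, and coverage of the stratified version was 0.935 in 600 runs.

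**5. Dependence on the balance.** With arms allocated at random regardless of centre, omitting centre gave coverage of 0.944 and a width of 1.451, against 0.951 and 1.344 with centre. The over-coverage comes from the stratification; the gain in precision from including centre remains without it.

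**The case against.** The strongest reply is that this is a condensed article. The Economic evaluation section names a family of methods and lists no covariates at all, not even baseline values, so it is silent on centre and does not exclude it. The imputation list names broad classes and does not mention treatment arm either, so it may not be exhaustive. This stands in part: a reader might infer that the authors decided to ignore centre, and the text does not show that. But the same article specifies the clinical random effects down to correlated intercepts and slopes, and what it describes for the economic analysis is a less precise analysis than the design supports.

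Four stronger readings are tempting and should not be made:

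- **That ignoring clustering makes the intervals too narrow.** That would apply if centres were randomised. Here individuals are randomised within centres, and the effect is the reverse.
- **That the cost-effectiveness outcome loses power.** At ICC 0.20 and 75 per arm, a test of the pain difference alone would have 78% power without centre and 83% with it. The article, however, plans ICERs, planes and acceptability curves, and states no economic test or power. No cost, ICER or acceptability curve was simulated.
- **That the 0.20 result carries over to costs and QALYs.** The 0.20 is a sizing input for pain; no ICC is given for the other outcomes.
- **That the clinical and economic intervals for 6-month pain would then agree.** One comes from a baseline-adjusted repeated-measures model, the other from a regression on multiply imputed data. They would still differ.

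Two features could also alter the net result. Participants who cannot read or write are allocated to only two of the three arms, so balance within centre will not be exact. Delivery is in online groups of up to 12, and unmodelled correlation within those groups would push intervals the other way. Both are separate matters; neither is a reason to omit the stratum.

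**Conclusion.** The point holds as a matter of precision. As described, the economic regressions, bootstrap and imputation list contain no centre term, and this makes the intervals conservative without biasing the differences. For the 6-month pain contrast the excess width is about 9 to 12% if the plan's ICC of 0.20 is right, 2 to 3% at 0.05, and under 1% at 0.01. For costs and QALYs the size is unknown and can only be assumed over the same range.

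These figures assume five equal centres, arms balanced within centre, normal outcomes and complete data; multiple imputation and the bias-corrected bootstrap were not simulated. The change is worth making because it is nearly free and loses almost nothing if the ICC is close to zero. The omission does not invalidate the economic evaluation.

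**What to change.** In the Economic evaluation section, or in the full analysis plan:

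1. Enter physiotherapy centre as four indicator variables in both the cost and the effect equation.
2. Refit that system in every bootstrap replicate, resampling within centre and arm, and take the ICERs, planes and acceptability curves from the adjusted differences. If some centre-by-arm cells are small, check that the intervals are not slightly narrow, as in the simulation with 15 per cell.
3. Add centre to the chained-equation imputation model.

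If the full plan already does this, a sentence saying so is enough. The cost is four degrees of freedom per equation out of 315 participants and a few lines of R code. Centre is the randomisation stratum, so no new data are needed.
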